**Figure 3 F3:**
[figure not shown]
Balance of baseline covariates across different levels of the instrumental variable, the proportion within the cancer referral network who received SABR with curative intent versus surgery. 6m, six months prior ;COPD, chronic obstructive pulmonary disorder; HFRS, Hospital Frailty Risk Score; SABR, stereotactic ablative radiotherapy.

The IV approach will report comparative effectiveness and cost-effectiveness across the overall eligible study population. The first stage models will estimate the probability of receiving SABR versus surgical resection given baseline covariates and the IV.^72^ The second stage outcome models will use the general linear models framework and choose the specific model according to whether the endpoint is binary (e.g., mortality at 3 years), continuous (e.g., costs) or time-to-event (e.g., time to death). All estimates will be reported with bootstrapped CIs that make appropriate allowance for clustering.

The IV approach will also report comparative effectiveness and cost-effectiveness according to prespecified subgroups including sex; age group; pre-existing cardiovascular disease or not; hospital frailty score (corresponding to fit, low or intermediate risk); Zubrod performance status (0–2), tumour stage, tumour histology and year of diagnosis.

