### Target trial design

We will emulate a target trial by conceptualising this non-randomised study as if it were an RCT in clearly defining the eligibility criteria, study population and treatment regimens (table 2).^43 47^ These definitions are informed by ongoing and prematurely closed RCTs comparing the effectiveness of SABR versus surgical resection for early-stage NSCLC.^9 10 15 16 49^ Even after applying the target trial eligibility criteria, it is likely that unobserved confounders (e.g., tumour location) will remain imbalanced between the comparison groups. We will use an instrumental variable (IV) analysis to reduce the risk of bias due to unobserved confounding^44 46 50^ (see the Analyses section for details).

**Table 2 T2:** Overview of the emulated target trial components and their definitions

Protocol component	Emulation protocol
Inclusion criteria	People with first primary NSCLC diagnosis (T1 – T2 N0 M0) between 1 January 2015 and 31 December 2020, according to ICD-10 C34 (all ICD-O-3 morphology codes except those between 8041 and 8045) who received SABR with curative intent or underwent surgical resection within 30 days before or 6 months after diagnosis (base case)
	Aged 18–79 years old if Zubrod performance status 0–2, age 80+if Zubrod performance status 0–1
Exclusion criteria	Synchronous lung cancerPregnancy at time of diagnosis
	Previous thoracic radiotherapy within 5 years prior to diagnosisPrevious metastatic malignancy within 5 years prior to diagnosis
	No surgery or radiotherapyOther types of radiotherapy as index treatment
Treatment strategies	Radiotherapy with curative intent: Stereotactic Ablative Radiotherapy (SABR)Surgical resection: Video-assisted or open thoracic lobectomy+/-mediastinal lymph node dissection (MLND); segmentectomy+/-MLND; wedge resection+/-MLND
Assignment procedure	Two approaches to address confounding: Randomisation will be emulated with an instrumental variable analysis that aims to balance observed and unobserved baseline prognostic measures between the comparison groups (base case analysis). The proposed instrument is the proportion of eligible patients treated with SABR versus surgical resection within the cancer network Randomisation will be emulated via a double robust method- inverse probability of treatment weighting with regression adjustment (alternative analysis)
Time zero	Date of treatment start

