Follow-up	Follow-up begins on date of treatment assignment (time zero) and ends 3 years after baseline (base case)
Outcome	Primary outcome: all-cause mortality at 3 years from the date of treatment receipt
	Secondary outcomes: all-cause and lung-cancer mortality at 3 months, 6 months, 12 months, 24 months, and 36 months; time to death; number of days in hospital in 12 months after treatment start; incremental costs; and incremental cost-effectiveness (incremental net health benefits).
Causal contrast of interest	Intention-to-treat effect (patients analysed according to their allocated treatment, regardless of whether they did not fully adhere to treatment or switched to other treatments)

NDRS, National Disease Registration Service; NSCLC, non-small cell lung cancer.

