#### Causal contrast of interest

The analysis will follow an intention-to-treat approach with individuals included in the analysis according to whether they received SABR or had surgical resection at time zero, irrespective of the treatments they received subsequently. Individuals will therefore continue to contribute to the analysis until they are censored by death or the end of the 3-year follow-up period (base case) or 31 December 2023 (alternative analysis).

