### Planned statistical analyses

#### Main analyses (base case)

For the main analysis (base case) we will use an IV to reduce the risk of confounding that is due to unmeasured baseline variables, such as tumour location, as well as measured confounders, such as age or cancer stage.^58^ The IV will exploit natural variation across the cancer networks and over time in the proportion of eligible individuals who had SABR rather than surgical resection (see figure 2). This natural variation implies that people with a similar prognosis at baseline will differ in whether they receive SABR or have surgical resection simply according to the cancer network or the time period in which they have treatment. The definition of cancer referral networks aligns with the ‘hub’ and ‘spoke’ model of care for lung cancer^68^ and comprises a surgical centre (the hub) with a multidisciplinary team who inform the decision of SABR versus surgical resection and the surrounding hospitals (the spokes) that refer individuals with NSCLC to the centre. The IV is the historic proportion of eligible individuals with NSCLC within each cancer referral network who had SABR versus surgical resection. This proportion is calculated for each individual for the six months before that individual starts either treatment.

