**Figure 2 F2:**
[figure not shown]
The proportion of eligible patients in each cancer referral network who had SABR with curative intent versus surgery in the NDRS pilot data (2015–2018). NDRS, National Disease Registration Service; SABR, stereotactic ablative radiotherapy.

A valid instrument must meet three main conditions.^58^ First, the instrument must predict the treatment received, which can be formally assessed.^69 70^ For the instrument to be of sufficient strength, the F-statistic summarising the association between the IV and the treatment received must exceed 100.^71^ In the NDRS pilot data, the corresponding F-statistic^70^ was 329. Second, the instrument must be independent of baseline covariates which are prognostic of the outcome of interest. This can be evaluated for the observed baseline measures. We found that the observed baseline variables were balanced across different levels of the instrument (figure 3). Third, the instrument must only have an effect on the outcomes through the treatment received, which cannot be evaluated empirically. If there were imbalances in measured covariates across levels of the IV this would raise concerns about the second and third IV assumptions. We will address this potential risk of confounding by adjusting for any residual differences in measured contextual and temporal confounders in the second stage (outcome) regression. These differences may pertain to variations in the quality of cancer care provided across the networks. By adjusting for these variables, we can make a weaker assumption that the IV, the proportion in the network who received SABR, does not have a direct effect on the outcome *after* adjusting for any differences in contextual variables pertaining to the quality of care and the time period.

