### Strengths and limitations

This study will assess the comparative effectiveness and cost-effectiveness of SABR versus surgical resection for early-stage NSCLC. By using national cancer registry data, this study identifies a large and diverse population that is directly relevant for clinical decision making. A key strength of this study is its ability to report results stratified by clinically relevant risk factors. Combining the target trial design with the IV analysis can help reduce bias from confounding by indication, enhancing the robustness of our findings.

The study protocol will have a similar design to the relevant RCTs, for example, ACOSOG 4099/RTOG 1021, STARS, ROSEL, VALOR, STABLEMATES, but also allow for appropriate representation of those subgroups underrepresented in trials. To enhance the clinical relevance and validity of the study, a clinical panel informed aspects of the study, including the eligibility criteria, treatment definitions, outcome measures and expected effect sizes.

A limitation of the study is that the national population-based cancer registry has limited detail on tumour location, so some individuals included, such as those with centrally located disease who undergo surgical resection, might not have been eligible for SABR. The linked NDRS registry data does not capture information on all outcomes of interest, including the toxicity of treatments, HRQoL or disease recurrence. For these outcomes, which are required for the CEA, we will draw on a review of the published literature. As with any non-randomised study, this study will make assumptions that cannot be tested from the data, but the alternative analyses will assess the robustness of the findings to the key assumptions made in the base case (main) analysis.

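### The instrumental variable estimate is presented as the effect in the whole eligible population, but the three conditions listed do not identify that effect when treatment effects vary between patients

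*Protocol article*

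**What the plan says.** **Target population.** Under Main analyses (base case), in the text after Figure 3, the article says "The IV approach will report comparative effectiveness and cost-effectiveness across the overall eligible study population". The objectives and the cost-effectiveness overview also name the overall population, alongside subgroups, as the level at which effects and net health benefits are reported.

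**Instrument.** "The IV is the historic proportion of eligible individuals with NSCLC within each cancer referral network who had SABR versus surgical resection". It is computed over the six months before each patient starts treatment, so it is a continuous proportion.

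**Conditions.** After Figure 2: "A valid instrument must meet three main conditions". Those given are prediction of treatment (with a pilot F-statistic of 329 against a threshold of 100), independence of prognostic covariates, and no effect on outcome except through treatment.

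**Estimation.** "The first stage models will estimate the probability of receiving SABR versus surgical resection given baseline covariates and the IV". A second-stage outcome model follows, chosen by endpoint type. The text does not name the estimator.

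**Causal contrast.** Table 2: "Intention-to-treat effect (patients analysed according to their allocated treatment". The section Causal contrast of interest includes patients "according to whether they received SABR or had surgical resection at time zero, irrespective of the treatments they received subsequently".

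**Limitation.** Strengths and limitations accepts that some included patients, "such as those with centrally located disease who undergo surgical resection, might not have been eligible for SABR".

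**The concern.** An instrument carries information about treatment effects only through patients whose treatment changes with it. Turning that information into an average over all eligible patients needs a further assumption, and the article gives the overall target without one.

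The article itself makes varying effects plausible. It plans subgroup results by eight factors: sex, age group, cardiovascular disease, frailty, performance status, stage, histology and year. Variation by measured factors can be modelled. Variation by unmeasured ones cannot, and the article names tumour location as an unmeasured confounder.

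At stake is whom the result describes. An effect weighted towards patients whose modality depends on local practice could be reported, and carried into net benefit, as applying to all eligible T1-2N0M0 patients. The inverse probability weighting analysis offered under Alternative analyses may average over a different population. A disagreement between the two could then reflect different target populations rather than unmeasured confounding.

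**Working it through.** **1. What the sample size section targets.** Inputs: 19.8% mortality, effect 7.5 points, 80% power, two-sided 5%, compliance c = 0.7, SABR share f = 520/2,887 = 0.180. The unpooled formula is N = (1.960 + 0.842)² × [f·p_surg(1 − p_surg) + (1 − f)·p_SABR(1 − p_SABR)] / [f(1 − f)·d²·c²]. It gives 2,885 against the printed 2,887 when SABR mortality is 19.8% and surgical mortality 12.3%. With 19.8% as the surgical rate, as the text has it, it gives 3,689. That mismatch is a separate matter. What matters here is the c² divisor: the plan sizes for an effect of treatment received and expects the instrument not to determine treatment in everyone.

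**2. What the three conditions deliver.** Take two instrument levels, low and high. Patients who have SABR at both levels, or surgery at both, contribute nothing to the outcome difference. Let π_C be the share moved towards SABR, with effect Δ_C, and π_D the share moved away, with effect Δ_D. The IV ratio is

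(π_C·Δ_C − π_D·Δ_D) / (π_C − π_D).

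- With monotonicity (π_D = 0) it equals Δ_C, the effect in the moved patients.
- Without monotonicity it need not be the effect in any defined group.
- It equals the overall average if effects are homogeneous.
- With a continuous instrument, monotonicity and support wide enough to cover all patients, marginal effects can be averaged to the overall effect.

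The F-statistic of 329 bears on relevance alone and selects none of these cases.

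**3. How far the two averages can differ (illustration).** Overall effect = s × 7.5 + (1 − s) × e, where s is the responsive share and e the effect in the rest, both assumed.

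| s | e = 0 | e = 15 points |
|---|---|---|
| 0.7 | 0.7 × 7.5 = 5.25 | 5.25 + 0.3 × 15 = 9.75 |
| 0.3 | 0.3 × 7.5 = 2.25 | 2.25 + 0.7 × 15 = 12.75 |

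The value s = 0.7 borrows the plan's compliance rate and 0.3 is a lower alternative. Neither is an observed share.

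**4. A simulated case.** Network SABR shares are assumed to run from 5% to 35%, giving 5% always SABR, 30% responsive and 65% always surgery. Assumed effects are −5, 0 and +10 points. Overall effect: 0.05 × (−5) + 0.30 × 0 + 0.65 × 10 = 6.25 points. Two-stage least squares on the simulated data gave about 0.2 points. The effects were chosen to make the gap visible; this is not a forecast.

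**5. A bound on support.** Expected SABR share is 3,000/18,000 = 16.7%. If the instrument is split at its median into equal halves, the two uptakes average 16.7% and neither is below zero. They can therefore differ by at most 2 × 16.7 = 33 points.

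**6. Patients outside the instrument's reach.** If the surgery group includes patients not eligible for SABR, they have surgery in every network. Their outcomes under SABR are not informed by the data, and any overall figure that covers them relies on assumption.

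**The case against.** The strongest reply is that the sentence may only contrast overall with subgroup reporting. The Introduction describes the comparison as one between patients who could have either modality, and Alternative analyses adds populations nearer equipoise. The article speaks of main conditions, not a complete list, cites its methods, and may leave assumptions to a fuller plan. These points moderate the criticism. They do not supply the link between the stated conditions and the stated population, and the untestable assumptions that are acknowledged say nothing about whom the estimate describes.

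Four stronger readings are tempting and are not supported:

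- *The IV identifies the effect only in practice-dependent patients.* The instrument is continuous and the estimator unnamed. Under homogeneity, or with adequate support and averaging of marginal effects, an overall effect could be targeted. The article neither shows nor excludes this.
- *The intention-to-treat label is wrong because, with "Randomisation will be emulated with an instrumental variable analysis that aims to balance observed and unobserved baseline prognostic measures", it should mean the effect of network practice.* The Causal contrast section defines it as treatment at time zero regardless of later treatment, which is a defensible use. Only the word for allocation in Table 2 is loose.
- *The surgery group contains patients who could not have had SABR.* The article says it may contain patients who might not have been eligible.
- *The F-statistic shows what fraction of patients would change modality.* Assuming a pilot of 8,000 to 12,000, R² = F/(F + N − 2) is 0.040 to 0.027. The SD of predicted SABR probability, √(R² × 1/6 × 5/6), is 0.074 to 0.061, so ±2 SD spans 1.9–31.5% or 4.5–28.8%. The text gives neither the pilot size nor the type of F-statistic. With an assumed design effect of 5 the lower limit falls below zero. Figure 2, which would show the actual spread, was not available for this check, so no such fraction should be reported as a property of this study.

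**Conclusion.** The point holds as a mismatch between the stated target population and the stated identifying conditions. With varying effects, relevance, independence and exclusion do not identify the average over all eligible patients; homogeneity, or monotonicity with sufficient support, is also needed. It is not shown that the analysis fails, because the estimator and the observed instrument range are not in the text. The size is therefore conditional. In the illustrations a 7.5-point effect in responsive patients is compatible with an overall effect of 5.25 to 9.75 points (responsive share 0.7) or 2.25 to 12.75 points (share 0.3), given 0 to 15 points in the rest. This should be corrected before results are reported, because it determines whom the effectiveness and net-benefit conclusions may cover.

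**What to change.** 1. In Main analyses (base case), state which further assumption links the IV estimate to the overall population: homogeneity, or monotonicity with support.
2. Report the range of instrument-predicted SABR probability, and the size and covariate profile of patients whose modality depends on network practice.
3. Unless the assumption or the support is shown, limit the effectiveness and net-benefit conclusions to that group, or label the overall figure as extrapolation.
4. Under Alternative analyses, note that the weighting analysis may target a different population, so a difference from the IV result is not by itself evidence of confounding.
5. In Table 2, replace the reference to allocated treatment with treatment started at time zero, in line with the Causal contrast section.

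The cost is some rewording, one descriptive table from data already planned, and possibly a narrower claim.

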### Cost-effectiveness analysis

#### Overview

We will assess the comparative cost-effectiveness of SABR versus surgical resection for individuals with early-stage NSCLC. The CEA will take a hospital perspective and report costs, outcomes and cost-effectiveness over a 3-year time horizon. This perspective and time horizon are anticipated to be sufficient to capture the important differences in mean costs and mean outcomes between the comparison groups. The CEA will incorporate individual-level resource use and mortality data from the linked NDRS data, combined with unit costs and health-related quality of life (HRQoL) estimates from the literature.^59^,^61^ The CEA will follow the assessment of comparative effectiveness in using IV methods to reduce the risk of residual confounding. We will report the net health benefits^62^ of SABR with curative intent versus surgical resection overall and for the subgroups of interest described in the Main analyses section.

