#### Outcomes for the CEA

We will calculate the number of life years from the date of treatment start up to 3 years (base case) and for the maximum observation period available (alternative analyses). The NRDS linked data will be used to identify cancer recurrence and disease progression based on diagnoses and procedures captured in subsequent hospital admissions, registration of new tumours and treatment receipt, including surgery, chemo-oncology, immuno-oncology therapy and radiotherapy using a novel approach developed for bowel cancer.^65^ The IV analysis will compare the adjusted proportions of cancer recurrences, common severe adverse events (eg, pneumonia, respiratory distress syndrome or failure and myocardial infarction)^66^ following SABR versus surgical resection. Pending these results, we will apply appropriate HRQoL estimates from the literature.^59^,^61^ For individuals who died of lung cancer, lower HRQoL will be assigned in the six months prior to death.

We will combine survival time with appropriate HRQoL estimates from the literature and use the ‘area under the curve’ approach^67^ to report quality adjusted life years (QALYs) at 3 years from treatment start. We will calculate the incremental net benefit by valuing the incremental QALYs (difference in mean QALYs for SABR vs surgical resection) with alternative threshold levels for cost per QALY gain, including those specified by NICE (eg, £20 000 and £30 000).

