#### Alternative analyses

We will conduct alternative analyses under four broad categories to check the robustness of the base case results. The first set of alternative analyses will pertain to the inclusion criteria to examine whether the results are robust to alternative inclusion criteria. For example, we will consider the combination of age and performance status suggested in the SABRTooth feasibility study protocol^11^ or performance status 0–1 as in VALOR^15^ to identify patients suitable for a trial comparing SABR versus surgical resection. We will also look at the impact of excluding observations who did not have either treatment within three (vs six months) of diagnosis. Both alternative inclusion criteria reflect an alternative definition of the population for whom there may be more equipoise between SABR and surgical resection. Second, we will consider the impact of COVID-19, for example by excluding individuals treated during the first wave of COVID-19 (1 February–30 June 2020). Third, we will consider analysis methods that make different causal assumptions to the IV analysis. For example, we will apply double-robust methods, such as inverse probability weighting with regression adjustment, which assumes no unobserved confounders.^73^

Fourth, for the CEA, we will consider alternative analyses that examine the impact of using the maximum available survival data in extrapolations to time horizons of 5 years, 10 years and the lifetime.^74^ We will also consider alternative sources for the requisite HRQoL data and alternative criteria for defining NSCLC recurrence.

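### Literature HRQoL values feed every QALY, but the stated interval method (bootstrap with allowance for clustering) provides no route for their uncertainty, so QALY and net-benefit CIs will be somewhat too narrow if those values are held fixed

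*Protocol article*

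**What the plan says.** The Strengths and limitations section states that HRQoL is not in the data: "The linked NDRS registry data does not capture information on all outcomes of interest, including the toxicity of treatments, HRQoL or disease recurrence". The cost-effectiveness Overview accordingly uses individual resource use and mortality "combined with unit costs and health-related quality of life (HRQoL) estimates from the literature".

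Outcomes for the CEA gives the construction: "We will combine survival time with appropriate HRQoL estimates from the literature and use the ‘area under the curve’ approach". It links HRQoL to recurrence and severe adverse events, whose proportions are to be compared between modalities, and assigns a lower value in the last six months of life to those who die of lung cancer. The values are not yet chosen: "Pending these results, we will apply appropriate HRQoL estimates from the literature". Incremental net benefit is then calculated at thresholds that include £20 000 and £30 000 per QALY. Table 2 lists incremental net health benefit among the secondary outcomes.

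On intervals, Main analyses (base case) has one sentence covering mortality, costs and cost-effectiveness alike: "All estimates will be reported with bootstrapped CIs that make appropriate allowance for clustering". On uncertainty in the HRQoL inputs, Alternative analyses has one sentence: "We will also consider alternative sources for the requisite HRQoL data and alternative criteria for defining NSCLC recurrence".

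**The concern.** A bootstrap of patients or referral networks reproduces the sampling variation of what was measured on them: survival, resource use, treatment and the instrument. A utility value taken from a paper is the same number in every replicate unless the analyst deliberately redraws it. The interval sentence names clustering as the only feature to be allowed for, and the article mentions no distribution for the HRQoL inputs.

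The planned scenarios do not fill the gap. Replacing one source by another moves the point estimate and leaves the width of the base-case interval as it was.

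At stake is the precision claimed for incremental QALYs and net benefit. The cohort is large (at least 18 000 expected), so patient-level sampling error is small. Error in the published values does not shrink with cohort size and can therefore be a visible share of the total.

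**Working it through.** The article states no QALY, utility, SE or interval width, so there is no figure of its own to reproduce. The check asks how much variance is omitted under stated assumptions.

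**Inputs from the article (Sample size calculations):** 3000 SABR and 15 000 surgery; compliance rate 0.7; 3-year mortality 19.8% after surgery.

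**Assumptions (not in the article):** SD of 3-year QALYs 0.5; SE of a published HRQoL value 0.02 to 0.05; event differences and durations as given below; design effect 1, then 4.

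**Step 1. Patient-only SE of incremental QALYs**

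SE = SD / sqrt(N × p × (1 − p) × c²) = 0.5 / sqrt(18 000 × 1/6 × 5/6 × 0.7²) = 0.5 / sqrt(1225) = 0.0143.

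With a design effect of 4 this doubles to 0.0286. A separate model (exponential survival, utility 0.75, SABR mortality 0 to 7.5 points higher, design effect 1 or 4) gives 0.016 to 0.035, so the order of magnitude is stable.

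**Step 2. Inflation when HRQoL error is added**

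Ratio = sqrt(1 + (e / SE)²), where e is the error in incremental QALYs caused by the HRQoL value.

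**Step 3. Event-based values, as Outcomes for the CEA describes**

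Here e = (HRQoL SE) × (duration in years) × (between-arm difference in the proportion with the event).

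| Value | e | Ratio |
|---|---|---|
| Six months before lung-cancer death, SE 0.05, 7.5-point difference | 0.05 × 0.5 × 0.075 = 0.0019 | 1.01 |
| Adverse event, 3 months, SE 0.05, 10-point difference | 0.05 × 0.25 × 0.10 = 0.00125 | 1.00 |
| Recurrence, 1 year, SE 0.02, 5-point difference | 0.02 × 1 × 0.05 = 0.001 | 1.00 |
| Recurrence, 2 years, SE 0.05, 10-point difference | 0.05 × 2 × 0.10 = 0.010 | 1.22 |

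Taking the first, second and fourth rows together as independent: e² = 0.0019² + 0.00125² + 0.010² ≈ 0.000105, ratio sqrt(1 + 0.000105 / 0.000204) = 1.23. With a design effect of 4 the same combination gives sqrt(1 + 0.000105 / 0.000816) = 1.06.

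**Step 4. A baseline utility common to both arms**

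Its error multiplies only the life-year difference (0 to 0.12 years in the exponential model). For SE 0.01 to 0.05 the ratio is 1.00 to 1.06; the top value is sqrt(1 + (0.1233 × 0.05 / 0.01755)²) = 1.06.

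**Step 5. Values that differ by modality for every patient**

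- 6 months, SE 0.02 to 0.05: e = 0.010 to 0.025, ratio 1.22 to 2.02; with a design effect of 4, 1.06 to 1.33.
- 3 years, SE 0.02: e = 0.06, ratio sqrt(1 + (0.06 / 0.0143)²) = 4.3.
- The exponential model gives 1.00 to 1.28 for a 3-month decrement and 1.3 to 8.7 for a 3-year one (SE 0.01 to 0.05, design effect 1 or 4).

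**Step 6. What this means for an interval**

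At a ratio of 1.22, a nominal 95% interval built on the patient-only SE reaches 1.96 / 1.22 = 1.61 true SEs either side, which is about 89% coverage. At 1.06 it reaches 1.85, about 94%.

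**The case against.** The strongest reply is that the article never says the HRQoL values are held fixed. Its interval sentence is compatible with redrawing them within each replicate, which is the remedy proposed here. The article is condensed, the HRQoL values are not yet selected, and input distributions are commonly left to a health economics plan that is not shown. This stands, and it means no error has been demonstrated. It does not remove the point: the article fixes one method for all estimates, and that method as described does not reach inputs from outside the data.

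A second reply is that HRQoL uncertainty is not ignored, since other sources will be tried and the limitation is openly stated. That is also true, and the choice of source may well be the larger uncertainty. But scenarios answer a different question from the one a CI answers.

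A reader might also infer more than the article supports:

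- **That the intervals definitely come from patient resampling alone and are definitely too narrow.** Both are inferences from silence.
- **That the SE is wrong by a factor of 2, 4 or more.** Those figures need an HRQoL difference applied to every patient in one arm for six months or three years. The article describes event-linked values and no modality-specific value for everyone. The 2.0 and 4.3 also ignore the clustering that the plan promises to allow for.
- **That a probability of cost-effectiveness will be overstated.** The article plans incremental net benefit and mentions no such probability.

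**Conclusion.** The point holds in conditional form, as an inexpensive improvement to a secondary economic outcome. If the literature HRQoL values are constants across replicates, the CIs for incremental QALYs and net benefit omit a non-negative variance term. The direction is therefore certain, given that condition.

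The likely size is modest. For the event-based values the article describes, the full SE of incremental QALYs is about 0 to 20% above the patient-only SE, and nearer the lower end once clustering is allowed for. This rests on an assumed QALY SD of 0.5, HRQoL SEs of 0.02 to 0.05, assumed event differences and durations, and the article's compliance rate of 0.7. A weaker instrument would enlarge the patient-only SE and reduce the ratio further. The ratios refer to QALYs; sampling error in costs also enters net benefit and would usually dilute them. Only sustained, modality-specific utilities for all patients would make the omission large, and the article does not specify those.

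The primary outcome, all-cause mortality at 3 years, and the other mortality results do not use HRQoL and are unaffected.

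**What to change.** Add to the interval sentence, or to Outcomes for the CEA, that in each bootstrap replicate:

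1. every HRQoL value is drawn from a distribution with its published mean and SE (for example beta for utilities, gamma for decrements), with correlated draws where values share a source;
2. QALYs and net benefit are recomputed with the drawn values;
3. the CIs for incremental QALYs and net benefit are taken from those replicates.

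Keep the alternative HRQoL sources ("We will also consider alternative sources for the requisite HRQoL data") as scenarios, each with its own draws. If the authors prefer fixed values, they should say so and label the QALY and net-benefit CIs as conditional on them.

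The cost is a few lines of code, the extraction of SEs along with the published means, and somewhat wider net-benefit intervals.
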